#### Mobile exercise test data

The original form is the acceleration a (m/s) of three axes (X, Y and Z) vector direction, respectively, rotation radian w (rad/s). The MATLAB (version R 2018a, MathWorks, USA) computer program will be used to perform Fourier transformation of the data, and acceleration and rotation radian measurements by smartphone will be converted to corresponding frequency, peak amplitude and speed date. Final phone test data will be presented as the amplitude and frequency of static tremors. Then, normal distribution tests will be conducted. Since the sample size is small (N<5000), the Shapiro-Wilk normal test will be used. P value>0.05 indicates a normal distribution, while p value<0.05 indicates a non-normal distribution.

According to normal distribution test date, if mobile phone exercise test data are normally distributed and the variance uniform, mobile phone exercise test data in patients with PD in different groups will be tested using with two sample independent t-tests. P value<0.05 will indicate if the exercise is statistically significant between groups. If the data are not normally distributed, non-parametric tests (median and Mann-Whitney U tests) will be performed for comparison. P value<0.05 in median tests will indicate if differences in central tendency scores between groups are statistically significant.

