### Sample size

This study is designed as a randomised controlled trial. The main outcome is the mean relief of upper limb static tremor after treatment. A review of previous studies showed that aerobic exercise could reduce upper limb static tremor amplitude by approximately 60%. It is estimated that the average tremor amplitude of the control group is approximately 76±136 mm, and the intervention group is expected to be reduced by 50 mm after training. The test level α is set at 0.05 (bilateral), the degree of certainty 1-β is set at 0.80 and the control:intervention group ratio=1:1. A sample size of 63 was calculated using *http://powerandsamplesize.com*. However, considering an abscission rate of about 15%, 72 patients with PD will be included.

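### Tremor amplitude is almost sure to fail the normality gate, after which two sections give conflicting tests, significance rests on the weak median test, and the measured baseline goes unused

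*Protocol article*

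**What the plan says.** The Sample size section of the protocol article defines the target: "The main outcome is the mean relief of upper limb static tremor after treatment". Its planning value for controls reads: "the average tremor amplitude of the control group is approximately 76±136 mm". Its planned effect is worded as a shift in mm: "the intervention group is expected to be reduced by 50 mm after training". It also cites a reduction of about 60% from earlier work.

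The subsection Mobile exercise test data sets the analysis. A Shapiro-Wilk test comes first, read as follows: "P value>0.05 indicates a normal distribution, while p value<0.05 indicates a non-normal distribution". If the data pass and variances are equal, the groups are compared by an independent two-sample t-test. Otherwise: "If the data are not normally distributed, non-parametric tests (median and Mann-Whitney U tests) will be performed for comparison". The only decision rule given for that branch is: "P value<0.05 in median tests will indicate if differences in central tendency scores between groups are statistically significant".

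The general Statistical analysis section gives a different rule for non-normal data: the Wilcoxon rank-sum test alone. That is the Mann-Whitney test under another name, and the median test is not mentioned there.

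Table 1 schedules the phone tremor test at baseline, week 9 and week 17. None of the between-group comparisons stated for amplitude uses the baseline value.

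**The concern.** Amplitude cannot be negative, and the planning SD is 1.8 times the mean. Such a variable cannot be close to normal, so the t-test branch exists largely on paper. What matters is the non-normal branch. There the protocol names two tests for one question, lets the weaker one carry the significance statement, and conflicts with its own general rule. If the median test and Mann-Whitney disagree, the two sections could support different conclusions on a primary outcome.

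The stated comparison is also unadjusted although baseline amplitude is measured. If amplitude varies much more between patients than within them, this discards information already paid for.

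**Working it through.** **The plan's own figure.** The stated inputs do not reproduce the sample size of 63. For a two-sided 5% test with 80% power, n per arm = 2 × (1.96 + 0.84)² × (136/50)² ≈ 116.1, so 117 per arm and 234 in total. This is a separate matter, noted because a change of analysis should not be used to explain it away.

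**Step 1: skew.** Inputs from Sample size: mean 76, spread 136, read as an SD (the protocol does not label it).
- CV = 136/76 = 1.789.
- A normal model would put Φ(−76/136) = Φ(−0.559) = 0.288 of patients below zero.
- A non-negative variable with this CV has skewness of at least CV − 1/CV = 1.789 − 0.559 = 1.23.
- A lognormal has log SD = √ln(1 + 1.789²) = 1.198 and skewness CV³ + 3CV = 11.1. A gamma has skewness 2 × CV = 3.6.

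**Step 2: which branch is used.** Shapiro-Wilk rejected lognormal samples of 31 in over 99.9% of runs. In every simulated scenario, lognormal and gamma, the gated rule (t-test if normal, median test if not) had the same power as the median test alone. The t-test branch was effectively never used.

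**Step 3: power at a 60% reduction.** Inputs: 31 per arm (72 × 0.85 ≈ 61 completers), outcome of mean 76 and SD 136, proportional effect, two-sided 5%. The baseline correlation ρ is not in the documents and is assumed.

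| Analysis | Lognormal | Gamma |
|---|---|---|
| Median test | about 63% | 13–18% |
| Mann-Whitney | 80–84% | 25–29% |
| Rank ANCOVA, ρ 0.5–0.7 | 91–97% | 34–47% |

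Read these to within a few points; a separate set of 1,500 runs per scenario gave 17–21%, 28–32% and 34–44% for the gamma column. At ρ = 0, rank ANCOVA roughly equals Mann-Whitney.

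**Step 4: power at the planned effect** (76 to 26 mm, ratio 26/76 = 0.342), 1,500 runs per scenario.

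| Analysis | Lognormal | Gamma |
|---|---|---|
| Median test | 77–78% | 20–22% |
| Mann-Whitney | 91% | 36% |
| Rank ANCOVA, ρ 0 / 0.5 / 0.7 | 91 / 96 / 99% | 37 / 44 / 60% |
| ANCOVA on plain log, ρ 0 / 0.5 / 0.7 | 93 / 98 / 99.7% | 25 / 30 / 43% |
| Unadjusted t-test in mm | about 70% | 51–54% |
| ANCOVA in mm, ρ 0 / 0.5 / 0.7 | 70 / 75 / 85% | 53 / 58 / 70% |

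Under the gamma, a log scale with a 1 mm offset gave 47–63% at ρ 0.5–0.7, so the offset removes most of the weakness of the plain log.

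**Step 5: cost of the median test.** Across these two effect sizes and both shapes, its deficit against Mann-Whitney in the 1,500-run scenarios runs from 28.0 − 18.1 ≈ 10 points to 83.5 − 63.6 ≈ 20 points. With no effect, rejection rates for all analyses were between about 3% and 5%.

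**The case against.** Several counter-arguments have force.

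- **The plan already contains a good test.** This stands in part. Mann-Whitney is named in both sections, and under a lognormal at the planned effect it already has about 91% power. It would be wrong to say that the plan offers only a median test. But the stated significance rule does not rest on Mann-Whitney.
- **A log-scale ANCOVA recovers the lost power at no cost.** A reader might infer this, but the documents give neither the shape nor the baseline correlation it needs. Under a gamma with the same mean and SD, plain log ANCOVA falls below Mann-Whitney at ρ of 0 and 0.5, because near-zero values gain too much influence. It also changes the effect from mm to a ratio.
- **Raw-scale analysis can win.** This stands: under the gamma, ANCOVA in mm beats rank ANCOVA. Under the lognormal it is clearly worse, so the best scale cannot be settled from the protocol.
- **The size of the median test's loss depends on settings.** With exactly 30 per arm its power changes markedly with the continuity correction (50–54% with, 71–74% without, for a 60% reduction under the lognormal). At 31 per arm the correction makes no material difference, so that size is used here.
- **The pre-test inflates false positives.** A reader might infer this too. The simulations show no inflation, and since the gate almost always rejects, the branch is nearly fixed in advance. The loose reading of p>0.05 as proof of normality therefore has little practical consequence here.
- **The main outcome is relief, which may mean change.** Change can be negative, so the non-negativity argument would not carry over directly. The analysis subsection does not say that change is compared; it refers to amplitude and frequency.
- **Baseline adjustment is commonly left to an analysis plan.** Fair as a general rule, and the protocol does say that changes in peak oxygen uptake and anaerobic threshold from baseline will be evaluated. For amplitude, however, specific unadjusted two-sample tests are stated, and the conflicting decision rule is in the text.

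**Conclusion.** The concern holds in this form: for a primary outcome, the stated rule for non-normal data is contradictory between two sections and rests significance on an inefficient test, and the planning figures make that branch nearly certain. The median test costs about 10 to 20 points of power against Mann-Whitney at the effects considered. Rank ANCOVA, or log ANCOVA with a fixed offset, beats both named non-parametric tests under both shapes if ρ is 0.5–0.7; with no baseline correlation, rank ANCOVA merely matches Mann-Whitney.

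This rests on 76±136 mm being the mean and SD of raw amplitude, on a proportional effect, on about 31 completers per arm, and on lognormal and gamma as plausible shapes. The ordering of the median test, Mann-Whitney and rank ANCOVA is more secure than the individual power figures. High power under the lognormal should not be read as support for a sample size of 63: that figure was derived for a mean difference in mm and is not reproduced by its own inputs.

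**What to change.** 1. Remove the Shapiro-Wilk gate and the median test for amplitude.
2. Make the general Statistical analysis section and the Mobile exercise test data subsection state the same rule.
3. Pre-specify one primary analysis of week-9 amplitude adjusted for baseline amplitude: either rank ANCOVA, or ANCOVA on log amplitude with a small offset fixed before data are seen. Keep Mann-Whitney as a sensitivity analysis.
4. With the log model, report a ratio with its 95% confidence interval; this is close in kind to the percentage reduction cited in the Sample size section.

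The cost is wording only, since Table 1 already collects the data. The drawback is that the effect is on a ratio or rank scale and no longer the mean difference in mm used for sizing. The gain depends on shape and baseline correlation, and any sample size justification on the new scale needs its own documented calculation.

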#### CPET test data

After subjects complete the CPET test, raw date will be saved. According to standardised principles of CPET data analysis, and the interpretation of Food and Drug Administration clinical trials in the Harbor-UCLA Medical Center,^33 34^ original breath-by-breath data from subjects will be sensed every second from the CPET system software. Then, average the data for 10 s and export the average data.^31 35^ The warm-up value is the average of the last 30 s of the warm-up period, the anaerobic threshold value is the data value of 10 s and the peak value is the average of 30 s during the extreme exercise. Anaerobic threshold analysis is performed using a v-slope method, that is, the mean value of 10 s of oxygen uptake when the CO_2_ emission rate is significantly accelerated relative to oxygen uptake rate during movement.^36^

## Discussion

PD not only reduces patients quality of life, but also generates a heavy economic burden for society and families. Upper limb static tremor is one of the main PD motor symptoms. Dyskinesia can also lead to decreased activity and aerobic capacity in patients with PD. Currently, non-drug therapy for PD mainly includes aerobic exercise and resistance training. Previous studies reported those methods were beneficial for tremor, bradykinesia, balance and quality of life in patients with PD.^37^ However, the effect of Qigong on PD static tremor and aerobic ability remains unknown.

Free radicals (OH)^38^ are a strong oxides that induce lipid peroxidation in unsaturated fatty acids and produce lipid peroxidation, which damages proteins and DNA and lead to cell degeneration and death. Oxidative stress^39^ represents an imbalanced state between oxidation and antioxidant effects in the body, which are important factors contributing to ageing and disease. Due to increased activity of B-monoamine oxidase in patients with PD, excessive free radicals oxidise and destroy cell membranes.^40^ At the same time, dopamine oxidation products in substantia nigra cells polymerise to form neuromelanin, which combines with iron to produce Fenton reactions and free radicals. Under normal circumstances, antioxidant molecules in brain cells are plentiful and include, glutathione (GSH), glutathione peroxidase (GSH-PX) and superoxide dismutase (SOD), thus free radicals generated by dopamine oxidation will not lead to oxidative stress.^41 42^ In PD, the substantia nigra is vulnerable to oxidative stress due to decreased ferritin and glutathione levels, and increased lipid peroxide, and iron ion concentrations.^41–43^ Previous studies^11 44^ reported that Zhan Zhuang improved SOD the activity levels in the body, prevented harm from superoxide free radicals and exerted positive roles fighting ageing, inflammation and immune disease, Therefore, the Zhan Zhuang may protect the substantia nigra in patients with PD by increasing SOD activity levels, reducing substantia nigra lesions, slowing down PD progression and improving overall symptoms in patients.

Currently, the generally accepted PD tremor mechanism in clinical practice is the induced-switch-regulation model proposed by Duval.^4^

Induced: Pathological activity in the basal nucleus striatum induces rhythmic cluster discharge activity in thalamic neurons via the excessive input of inhibitory signals to thalamic cells, and changes the discharge mode.

Switch: Oscillations in internal and external networks of the thalamus combine and cause oscillations to continuously integrate and strengthen until they reach tremor production threshold values.

Regulation: After PD tremor-related oscillations are introduced to the cerebellum, it processes oscillation as random movements and adjusts tremors to ensure stability in oscillation activities, such as frequency and amplitude. Tremors transmitted to the cerebral cortex are then transmitted to the periphery via the cortical-spinal cord pathway in the form of oscillations, and are finally manifested body tremors. Yang *et al*,^45^ based on data from basal ganglia injury mice and rats models, reported that exercise training reduced over-activation of basal ganglia cortical circuits, thereby weakening tremor signal transmission, and alleviating tremors. Recent studies also reported these animal models were applicable to humans.^46^ Kadkhodaie *et al*^15^ observed that upper limb centrifugal exercises effectively reduced upper limb tremor amplitude in patients with PD. Zhan Zhuang as an aerobic exercise may also reduce tremors at the motor level.

PD tremor is influenced by attention and stress levels.^47^ Previous studies reported that tremors were intentionally attenuated when attention was focused on them, and that PD tremors were is amplified by stress.^48^ Wang^49^ using nuclear magnetic resonance to analyse tremor subtypes in patients with PD, observed that the brains of tremor subtypes in patients with a wide range of functional connection between the frontal lobe and cerebellum, and UPDRS score III movement and the cognitive function score also existed significant correlation, that movement function and cognitive function in patients with PD has a high degree of correlation. DA substitution therapy also alleviated some motor characteristics in PD, but the observed beneficial effects on cognitive function were small.^50^ Several studies^21 51 52^ reported that Zhan Zhuang enhanced the attention and cognitive ability of adolescents and the elderly. Yiyue Chen^53^ observed that Zhan Zhuang exercises increased P3 wave amplitude in frontal, central and top regions, with a shorter incubation period when compared with baseline. P3 wave amplitude reflected the allocation of neural electrical resources, and latency which was related to the speed of stimulus classification. These results suggest that station post affected neural electrical processing related to cognitive control, by changing neural electrical resource allocation and stimulus classification speeds, thereby affecting cognitive function. Therefore, the station post may indirectly improve tremor performance by enhancing cognitive ability in patients.

Executive control is a general control mechanism where individuals coordinate different cognitive processes and resources to ensure their cognitive system implements specific goals in a flexible and optimised way when completing complex cognitive tasks. Executive control also coordinates brain commands and muscle movements. Yang *et al*^54^ conducted a 1-year Zhan Zhuang exercise in healthy college students, and observed that EEG activity coefficients in students who participated in Zhan Zhuang exercises were generally decreased, and that EEGs showed a high synchronisation trend. Whole brain ordering was improved, and brain activities were more coordinated and synchronised. Fang^55^ reported that Zhan Zhuang exercised the muscles of the whole body statically, provided benign stimulation to the brain and adjusted the disorder of excitement and inhibition of the cerebral cortex. Jianguo^56^ also confirmed that Zhan Zhuang improved subject response speeds and accuracy, and also improved the executive control levels in the brain. Zhan Zhuang combines body and mind, it focuses on controlling the body with the mind, and mobilising muscle groups in the trunk and limbs to participate in this process.^21^ This body and mind combination stimulates the nervous system and increase its sensitivity, ensuring more efficient and precise muscle control. Additionally, Zhan Zhuang places the body in a stressed state of postural control for long periods, with previous clinical studies showing that stress significantly affects neural plasticity.^56^ Thus, higher levels of executive control and finer, more efficient postural control may benefit PD tremor relief.

Guo^21^ observed that B cell receptor and NF-κB signalling pathways were significantly enriched in college students after Zhan Zhuang, suggesting the technique may enhance in vivo immunity and improve inflammatory microenvironments by activating B cell receptor signalling and improving T lymphocyte levels, or regulating NF-κB signalling. Regulating valine, leucine and isoleucine metabolism, prevents excessive glutamate accumulation, increases astrocyte and 5-hydroxytryptamine levels, and prevents neuronal necrosis and apoptosis. The specific regulation of the lysosomal pathway mediates autophagy levels, improves neuron survival rates and alleviates depression and improves adverse psychiatric symptoms. Several studies^21 56–61^ reported that the station post significantly improved blood flow, improved the inflammatory environment and possibly enhanced immunity.

### Ethics and dissemination

This study has been approved by the Ethics Committee of Shandong University of Traditional Chinese Medicine (Approval Number: 2021–025-KY). The results of this study will be published in a peer-reviewed journal, and trial participants will be informed via email or phone calls.
